### Trial status

Data collection is ongoing but the randomisation ratio has now been increased to 4:1 in favour of the intervention, following lower than expected consenting rates within the first 3 months of recruitment.

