## Methods/design

### Design

A single-stage phase II trial will test whether PN is likely to meet the basic level of efficacy (in this case by increasing uptake), is practical and acceptable within a UK setting and is therefore worthy of further investigation in a large-scale RCT [24]. To enhance the opportunity to conduct PN with individuals who do not confirm or attend their appointment, while keeping SSP workload to a minimum, a randomisation ratio of 2:1 will be used in favour of the intervention group (vs. usual care). The aim of the trial is not to make a direct comparison between the intervention and control groups but rather to consider the level of uptake in the PN group, while also assessing patients’ acceptability and willingness to be randomised. The CONSORT diagram is shown in Fig. 1.

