### Recruitment and setting

Recruitment will be conducted through the South of Tyne Screening Centre. The Screening Centre operates across three sites with one site, South Tyneside District Hospital (STDH), involved in this current study. Approximately, 40 people each week are invited to have BSS at STDH. All individuals invited for BSS at STDH will also be invited to take part in this study (see Fig. 2). There are no study exclusion criteria; however, only individuals who return a study consent form with their contact details, including telephone number(s), will be able to participate in this study. Recruitment will occur over a 6-month period.

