On receipt of each consent form, the RN will consult a pre-generated randomisation list to determine which study group each participant should be allocated to. Two randomisation lists (one for each gender) will be generated by a medical statistician, who will randomly allocate participants to receive either PN or usual care with a ratio of 2:1 favouring the intervention. It is not possible to blind the RN and SSPs to each participant’s study group allocation. However, the participants themselves will only know the group they have been allocated to when they receive either a navigation phone call or their end-of-study questionnaire (ESQ): the ESQ will be accompanied by a cover letter thanking them for their participation and informing them of their group allocation.

The RN will work with University College London (UCL) researchers and SSPs and use the BCSS to document all activities of consenting participants on a database devised for this study (e.g. group assignment, original appointment date and subsequent changes made, attendance status, date of ESQ mail out, and date of receipt of completed ESQ). This will allow the RN to monitor who is eligible for PN and to obtain important information for establishing the feasibility of the study design and expectations for the larger RCT.

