### Planned analyses

#### Primary analysis

The overall recruitment and uptake rates by trial arm will be described; the study is not powered to make a direct comparison between arms but will help inform sample size requirements for a phase III trial.

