#### Quantitative analysis

Data collected on the study database and from returned non-participation postcards will be analysed and mainly reported as descriptive data (e.g. attendance rates, time for return of ESQs, number of people selecting specific reasons for non-study participation). The ESQ data will be analysed using a mixture of descriptive and inferential statistics including chi-square analysis and linear and logistic regression so that predictors of attendance and non-attendance can be investigated, as can between group differences in views, attitudes, knowledge and satisfaction with BSS. Results will be presented with a 95 % confidence interval.

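### The allocation ratio rose from 2:1 to 4:1 during recruitment, but the planned between-arm summaries and tests make no provision for allocation period (low severity)

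*Protocol article*

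**What the plan says.** The Abstract, Design and Procedure sections of the protocol article set allocation at 2:1 in favour of patient navigation (PN). Under Procedure, "Two randomisation lists (one for each gender) will be generated by a medical statistician", and a single ratio is given for both. Recruitment and setting states "Recruitment will occur over a 6-month period".

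The Trial status section then reports that "the randomisation ratio has now been increased to 4:1 in favour of the intervention". The reason it gives is that fewer people than expected had consented in the opening three months. It gives no exact date for the change and does not say whether both gender lists changed together.

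On analysis:

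- Design: "The aim of the trial is not to make a direct comparison between the intervention and control groups". The primary outcome is a count of navigated non-attenders in the PN group who then attend.
- Primary analysis: "The overall recruitment and uptake rates by trial arm will be described". The same sentence says that the study lacks the power for a direct comparison and will inform the phase III sample size.
- Quantitative analysis: the end-of-study questionnaire (ESQ) data are to be analysed by methods including "chi-square analysis and linear and logistic regression". Group differences in views, attitudes, knowledge and satisfaction are among the stated targets, with 95% confidence intervals.
- Economic analysis: the cost of PN is set against that of usual care.

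None of these analysis sections mentions the ratio change, allocation period or the gender lists.

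**The concern.** When the ratio changes part-way, people consenting later are more likely to be in the PN arm than people consenting earlier. Randomisation then protects a comparison within each ratio period, but not one that adds the periods together. If attendance, attitudes or the mix of people consenting shifts over the recruitment period for reasons unrelated to navigation, part of that shift appears as a difference between arms.

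Some drift is plausible, though none is documented. Consent was running below expectation when the ratio was changed, and the limitations section says that the consent process may select more activated individuals.

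What is exposed is the set of secondary between-arm results: the ESQ contrasts, the cost contrast, and any difference that a reader takes from the described uptake rates when planning phase III. A chi-square test on a two-way table has no place for allocation period, so that named method does not fit a trial with two ratios.

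**Working it through.** **The plan's own figures.** From the Sample size section: 960 × 0.40 = 384 participants; 384 × 0.30 = 115.2, given as 116 non-attenders; 116 × 2/3 = 77.3, given as 77 allocated to PN. These reproduce, and they assume 2:1 throughout.

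**Inputs.** From the document: PN probability 2/3 before the change and 4/5 after it; usual-care probability 1/3 and 1/5; planned N = 384; predicted attendance 70%. Assumed, because the document gives neither: the recruitment split before and after the change, and the size of any drift.

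**Share of each arm from the 4:1 period, equal split.**

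- PN: 0.800 / (0.800 + 0.667) = 0.545
- Usual care: 0.200 / (0.200 + 0.333) = 0.375
- Difference: 0.545 − 0.375 = 0.170

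**Bias in an unadjusted contrast** = drift common to both arms × this difference.

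| Assumed drift (points) | Bias (points) |
|---|---|
| 5 | 0.85 |
| 10 | 1.70 |
| 20 | 3.41 |

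**Sensitivity to the split.**

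- Later recruitment at 0.7 times the earlier level: 0.560/1.227 − 0.140/0.473 = 0.161.
- At 1.3 times: 1.040/1.707 − 0.260/0.593 = 0.171.
- With 30% recruited before the change the difference is 0.154; with 70% it is 0.135.
- The maximum over all splits is 0.172, so a 10-point drift cannot give more than about 1.7 points.

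**Against sampling error.** With N = 384 and an equal split, the PN arm is 128 + 153.6 = 281.6 and usual care is 64 + 38.4 = 102.4. For a 70% proportion in both arms, the standard error of the difference is √[0.7 × 0.3 × (1/281.6 + 1/102.4)] = 0.053, so the 95% half-width is about 10.4 points. If low consent halved the sample to 192, it would be about 14.7 points. These figures count every participant; ESQ analyses depend on returned forms and will be less precise.

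**Sex.** If both lists carry the same ratio at each time and the sex mix is constant, the imbalance in sex between arms is 0. If the share of one sex moved from an assumed 40% to 60%:

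- PN: (128 × 0.4 + 153.6 × 0.6) / 281.6 = 50.9%
- Usual care: (64 × 0.4 + 38.4 × 0.6) / 102.4 = 47.5%

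The 3.4-point imbalance arises only through period, and stratifying by period removes it.

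**Primary outcome.** It is a count within the PN arm set against 35, with no usual-care term. The mechanism above has nothing to act on there.

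**The case against.** The case against is substantial, and much of it stands.

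- **Uptake is described, not tested.** The design disclaims a direct comparison, and the decision rule uses the PN arm only. A reader might infer that the decision to proceed is biased; the documents do not support that.
- **Pooling is not stated.** A reader might infer that the two periods will be combined without adjustment and the sex stratification ignored. The article says neither. The regressions can carry period and sex, and covariate lists are commonly left to an analysis plan that is not shown. What remains is that the article names a chi-square test and overall rates by arm, both of which suit a single fixed ratio, and then reports a second ratio without revisiting them.
- **Sex is not confounded with arm if both lists share a ratio.** This stands; omitting sex would then mainly cost precision. Whether the lists changed together is not stated.
- **Changes in how practitioners navigate are a different matter.** Usual-care participants receive no navigation call, so such a change alters PN outcomes only. It makes the PN result an average over a changing intervention, not a spurious difference from calendar imbalance. The 0.17 factor applies only to drift common to both arms.
- **The bias is hypothetical and small.** No drift is documented, and sampling error dominates for drifts of the sizes considered. It would therefore be too strong to say that every arm contrast is distorted.

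**Conclusion.** The point holds in a limited form. The ratio change associates arm with calendar period, and the article plans between-arm ESQ and cost analyses and overall uptake by arm without providing for it. An unadjusted contrast would carry at most about 0.17 of any drift common to both arms. The 1.7-point figure rests on an assumed 10-point drift and an assumed equal recruitment split, and compares with a half-width of 10 points or more. For costs, the same factor applies to a common drift in mean cost. The primary count and the 35-attender rule are untouched, and sex matters mainly for precision provided that both lists changed together. Severity is low. It is worth acting on because the bias is avoidable, data collection was still under way when the article was written, and the remedy uses the groups by which the trial already randomises.

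**What to change.** Add to the planned analyses:

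1. Define allocation period (2:1 or 4:1) by the list from which each participant was allocated, not by appointment date. State when the ratio changed and whether both gender lists changed together.
2. Stratify or adjust the between-arm ESQ and cost contrasts by allocation period, with sex as the randomisation stratum. Use Mantel-Haenszel tests and differences in place of the crude chi-square for arm comparisons, and put period and sex terms in the linear and logistic models.
3. Show uptake by arm within each allocation period beside any overall figure, so that phase III planning can draw on comparisons protected by randomisation.

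The cost is wording and minor extra analysis. Sex is known from the list used, and period follows from the date of the change, so no new data from participants are needed. The strata become somewhat sparser: under the equal split, usual care in the 4:1 period is expected to hold about 38 people at N = 384, or about 19 at N = 192, before division by sex. Mantel-Haenszel methods tolerate this.

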## Discussion

BSS offers the unique benefit of reducing CRC incidence as well as mortality, but this benefit can only be realised through uptake of the procedure. Within the first 14 months of the BSS programme’s launch, 21,187 invitations were sent out to eligible people across six pilot centres in England and the overall uptake was 43 % [8]. Although this was higher than expected in the early stages of the programme’s national roll-out, a need to proceed with interventions to boost uptake and reduce socioeconomic inequalities was highlighted [8]. Within the South of Tyne Screening Centre specifically, a below average uptake of only 37 % was reported, promoting itself as a key centre in which to base intervention initiatives.

Incorporating PN within the NHS BCSP, and providing a more personal and interactive way of communicating information about BSS, seems likely to circumvent many of the barriers associated with CRC screening. As part of their role as patient navigator, SSPs will have the opportunity to communicate the benefits of BSS more effectively and help to manage the feelings and fears associated with cancer screening and diagnosis, alongside access to care and other logistical issues. While navigation has been shown to work in the USA, its integration into the UK system requires investigation not only from a theoretical standpoint but also a practical one. This study not only aims to assess the acceptability of PN but also how it can be implemented within the system.

### Potential limitations, challenges and risks

Unfortunately, the telephone numbers of people eligible for BSS are not readily available within the programme and are only provided to SSPs through the appointment confirmation process. For this reason, and to adhere to research ethical standards, we will have to obtain consent to take part in this study and, as part of the consent process, specifically request the provision of an individual’s telephone number(s). It is possible that the consent process will represent a barrier and ultimately restrict the intervention to more ‘activated’ individuals, thereby introducing a selection bias. However, we have taken this into consideration and have assumed a higher uptake rate (70 %) within our sample compared to the general population.

Furthermore, there is a risk that people will mistake the consent for the study as confirmation of their future attendance at a BSS appointment which could negatively affect the BSS invitation process. As a result, we will closely monitor the impact of the study invitations on BSS uptake.

An additional limitation is that the PN training session and related manual will be developed and delivered by non-PN experts, which may lower the extent to which SSPs accept and identify with the PN intervention and their confidence to perform it.

### Conclusion

The results of this feasibility study will be instrumental in deciding whether a proposal will be made to conduct a large-scale RCT of the PN intervention in the BSS programme, in England. If PN was subsequently shown to be cost-effective at increasing uptake of BSS, NHS policies could be modified to implement PN as a standard service. Another important part of this feasibility study will be to identify barriers associated with BSS. Disseminating the findings from this study will therefore facilitate the development of additional strategies to increase uptake of BSS.

## Abbreviations

BCSP: Bowel Cancer Screening Programme
BSCC: Bowel Cancer Screening System
BSS: Bowel Scope Screening
CRC: Colorectal cancer
DNA: Did not attend
EQ-5D-5L: EuroQol-5 Dimensions Scale (5 level)
ESQ: End-of-study questionnaire
FS: Flexible sigmoidoscopy
gFOBt: Guaiac faecal occult blood test
ISRCTN: International Randomised Controlled Trial Number
NHS: National Health Service
PIS: Participant information sheet
PN: Patient navigation
PSS: Personal Social Services
QALY: Quality adjusted life year
RCT: Randomised controlled trial
RN: Research Nurse
SSP: Specialist Screening Practitioner
STDH: South Tyneside District Hospital
UCL: University College London
